## Abstract

**Background:**

Essential tremor (ET) is the most common neurological movement disorder with few treatments and limited therapeutic efficacy, research into noninvasive and effective treatments is critical. Abnormal cerebello-thalamo-cortical (CTC) loop function are thought to be significant pathogenic causes of ET, with the cerebellum and cortex are common targets for ET treatment. In recent years, transcranial magnetic stimulation (TMS) has been recognized as a promising brain research technique owing to its noninvasive nature and safety. In this study, we will use left M1 cortex continuous theta-burst stimulation (cTBS) combined with right cerebellar hemisphere 1 Hz repetitive transcranial magnetic stimulation (rTMS) dual-target stimulation to explore the Safety, feasibility and efficiency of this dual-target stimulation mode, and the mechanism of its therapeutic effect.

**Methods:**

Twenty-four patients with ET will be randomly assigned to three groups: dual-target stimulation, single-target stimulation, or sham stimulation. The single-target stimulation group will receive stimulation of the right cerebellar hemisphere for 10 days, whereas the dual-target stimulation group will be given stimulation of both the left M1 cortex and the right cerebellar hemisphere. The sham stimulation group will be given sham stimulation for 10 days. Tremor will be assessed using both the subjective The Essential Tremor Rating Assessment Scale (TETRAS) and objective accelerometer-based tremor analysis. at baseline (before stimulation), after the first, fifth, tenth days of treatment (D1, 5, 10), 24 h after 10 days of treatment (D10-24 h), and 1, 2, 3, and 4 weeks after stimulation (W1, 2, 3, 4).

**Discussion:**

This is a Phase 2 randomized, controlled, patient-assessor blinded clinical trial. The goal of this study is to investigate the Safety, feasibility and efficiency of TMS for the treatment of ET.

## Introduction

1

Essential tremor (ET) is one of the most common movement disorders affecting approximately 1% of the global population. The prevalence of ET increases by 74% every 10 years of age (1). ET is characterized by postural or action tremor in both upper limbs (2), and more than half of the patients report that tremor interfered with their everyday lives and jobs (3) and may become disabling (4). As China’s population ages, ET has become a chronic disease that can progressively worsen and affect the quality of life of patients (5–7).

The treatment for ET is limited (8, 9). Nothing available slows its progression, and the symptomatic drug benefit decreases with time. Propranolol and primidone are first-line medications with adverse effects, low patient compliance, and poor efficacy for refractory ET (10). With advancements in biomedical engineering and stereotactic technology, ET patients with severe symptoms can be treated with stereotactic ablation of the brain nuclei and deep brain stimulation (DBS) (11, 12). The ventral intermediate nucleus of the thalamus (Vim) (13, 14) is the most common target in treating ET, other potential targets, such as the subthalamic nucleus (STN) (15), the internal segment of the globus pallidus (GPi) (16), and the posterior subthalamic area (PSA) (17, 18) are also considered for their potential therapeutic benefits in DBS procedures. However, this treatment is invasive and costly (19), and the impact may fade with time (20).

Transcranial magnetic stimulation (TMS) has emerged as a noninvasive electrophysiological technique at the end of the twentieth century and has been used since its introduction (21). The TMS mechanism is as follows, a brief electric current is sent via a magnetic coil, generating a temporary high-intensity magnetic field that stimulates or inhibits parts of the brain beneath the coil (22). It is now widely utilized in the study, diagnosis, and treatment of neuropsychiatric diseases, such as neuropathic pain, depression, and Parkinson’s disease, but its use in ET treatment is still in the experimental stage (23).

Functional abnormalities of the cerebello-thalamo-cortical (CTC) loop are considered significant pathophysiological causes of ET (24), the cerebellum and cortex are currently common targets for ET treatment. TMS is a noninvasive and safe neuromodulation modality, has been used in several studies in the past. The use of repetitive transcranial magnetic stimulation (rTMS) (25–29) and continuous theta burst stimulation (cTBS) (30–33) to treat ET has been studied in several studies; However, given the different study designs, number of included cases, and stimulation modes, there are no consensus results. In this randomized, controlled, patient-assessor blinded clinical trial, we will use the left primary motor cortex (M1) area combined with the right cerebellar hemisphere as our dual-target transcranial magnetic stimulation, to preliminarily observe the safety, feasibility and efficiency of this stimulus pattern and to discover the possible mechanism of TMS on ET, with the aim of informing future larger-scale studies. We hope that dual-target stimulation will improve the stability of study treatment results.

Accordingly, we hypothesize that dual-target TMS therapy for ET is not only safe and feasible but also effective in alleviating tremor symptoms by modulating specific neural pathways.

## Methods

2

### Study design

2.1

This is a Phase 2 clinical trial designed to evaluate the efficacy and safety of dual-target TMS for the treatment of ET. The study is randomized and controlled, incorporating blinding for both patients and assessors. Patients will be screened for study participation within study enrollment. All participants will be evaluated via neurological examination, The Essential Tremor Rating Assessment Scale (TETRAS), electromyographic and accelerometric recording, and magnetic resonance imaging (MRI). The participants will be then randomly assigned to one of three groups: dual-target stimulation group, single-target stimulation group or sham stimulation group. We will examine the patients’ vital signs before and after each day of treatment and record daily treatment completion and adverse event occurrence. Electrophysiological detection and TETRAS will be performed at baseline, after the first, fifth, tenth day of treatment (D1, 5, 10), 24 h after 10 days of treatment (D10-24 h), and at 1, 2, 3 and 4 weeks (W1, 2, 3, 4) after stimulation.

MRI will be carried out at baseline, D10, and W4 (Table 1). Recruitment for this study is ongoing at the time of submission.

**Table 1 tab1:** Study schedule.

Procedure	Screening	Treatment				End	Follow-up			
Time point	D 0	D1-B	D1-A	D5-A	D10-A	D10-24 h	W1	W2	W3	W4
Basic										
Demography	✓									
Eligibility	✓									
Vital signs	✓	↔				✓	✓	✓	✓	✓
Informed consent	✓	↔				✓	✓	✓	✓	✓
Assessment										
TRETRAS		✓	✓	✓	✓	✓	✓	✓	✓	✓
Tremor analysis		✓	✓	✓	✓	✓	✓	✓	✓	✓
MRI	✓				✓					✓
Trial evaluation										
Adverse event			↔			✓	✓	✓	✓	✓
Safety evaluation			↔			✓	✓	✓	✓	✓

TRETRAS, The Essential Tremor Rating Assessment Scale; MRI, Magnetic Resonance Imaging; D0, Days before treatment; D1-B, Before the first day of treatment; D1-A, After the first day of treatment; D5-A, After 5 days of treatment; D10-A, after 10 days of treatment; D10-24 h, 24 h after 10 days of treatment; W1, One week after treatment completion; W2, Two weeks after treatment completion; W3, Three weeks after treatment completion; W4, Four weeks after treatment completion.

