### Accelerometer-based tremor analysis

2.4

Patients will be positioned in a comfortable chair equipped with armrests, and both upper limb tremor movements will be recorded utilizing a multi-sensor signal accelerometer (chip model: MPU6500). The device will be affixed to the dorsal surface of the metacarpal bones of both hands, enabling the capture of resting tremor (the patient will be instructed to relax and rest their hands on the chair armrests), postural tremor (two specific poses will be required: one with the arms extended forward and parallel to the ground, and the other maintaining a wing-beat posture), and kinetic tremor (assessed through the finger-nose test). Each movement will be recorded for 20 s, with tremor measurements repeated twice at each time point. The average of the two recordings will subsequently be calculated.

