#### Primary outcome

2.7.1

The primary outcome measure will be the mean change from baseline over the course of 4 weeks (at days 1, 5, 10, D10-24 h, then at weeks 1, 2, 3, and 4). This assessment will focus on the average tremor score derived from the TETRAS. The TETRAS (45) is a widely utilized instrument for evaluating the severity of ET and is employed to assess the remission and recovery of ET following TMS. The scale comprises a 12-item section that evaluates activities of daily living and a 9-item section that assesses tremor severity. Each item is rated on a scale from 0 to 4, with higher scores indicating greater severity.

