## Statistical analysis

5

In this study, we will conduct an analysis of the data utilizing the principles of modified intention-to-treat (ITT) analysis, which will encompass patients who have completed a baseline assessment of the primary outcome indicators. Safety analyses will be performed on all patients who have received at least one session of TMS. Continuous variables will be expressed as the mean ± standard deviation (SD) or median (25th percentile, 75th percentile), while categorical variables will be presented as percentages (%). For the assessment of baseline characteristics, continuous variables will be analyzed using One-way ANOVA (normal distribution) and Kruskal-Wallis H test (non-Gaussian distributions). Categorical variables will be evaluated using Chi-square or Fisher’s exact tests. The primary outcome measure will be the mean change from baseline over a period of 4 weeks, assessed at days 1, 5, 10, D10-24 h, then at weeks 1, 2, 3, and 4, specifically focusing on the average tremor score derived from the TETRAS. We will employ generalized estimating equations (GEE) for repeated measures within the modified ITT population. Additionally, sensitivity analyses will be conducted on the primary outcome, considering age, sex, disease duration, and baseline tremor score as covariates. Effects will be expressed as estimates along with 95% confidence intervals (CIs). GEE will also be applied to analyze secondary outcome measures, including the mean change in tremor power, amplitude, and frequency as recorded by accelerometers.

For data that is randomly missing between TMS sessions, where the missing data constitutes less than 5% of the sample, we will employ the last observation carried forward method to impute the missing values. Additionally, sensitivity analyses will be conducted to evaluate the impact of these imputations on the study outcomes. Conversely, missing data resulting from early dropouts (before 4 weeks) will not be imputed, as this data is not considered to be missing at random. Instead, these instances of missing data will be censored at the date of the participant’s last visit. All statistical analyses will be performed using IBM SPSS version 27.0, and *p*-values less than 0.05 will be considered statistically significant (two-tailed).

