cTBS uses rapid pulse patterns to quickly inhibit targeted brain areas (51), while low-frequency rTMS provides more lasting effects, suitable for long-term modulation (52). We hypothesize that combining these TMS techniques can yield complementary benefits. Chuang et al. (32) found that cTBS suppresses motor cortex excitability in ET patients and reduces tremor amplitude. Batra et al. (33) showed that cTBS significantly improves tremor symptoms by increasing the contralateral silent period (cSP). Gironell et al. (25) and Popa et al. (29) reported tremor improvements after rTMS stimulation of the cerebellum. However, data on the effects of noninvasive brain stimulation techniques applied to the cerebellum and motor areas of ET patients show variability in their effects on tremor (53, 54). Specifically, there is a significant degree of variability among individuals. Olfati et al. (28) found no significant improvement in the overall tremor score with rTMS compared to sham stimulation on days 5, 12, or 30 after treatment. In contrast, Popa et al. (29), using the same stimulation protocol, observed a significant and lasting reduction in all aspects of tremor. It is important to consider that ET is a highly heterogeneous disorder with potential inter- and intra-individual differences, where factors such as anxiety (55), fatigue (56), and caffeine consumption (57) can all influence the severity of tremors. Furthermore, the placebo effect is a concern that should not be overlooked; Shin et al. (27) found that there was an improvement in tremor scale scores regardless of whether the stimuli were real or sham. The cerebellum and cortex are the most popular targets for stimulation in TMS studies aimed at treating ET. Previous findings suggest that the outcomes of TMS for ET are highly variable, and we speculate that the use of double-target stimulation may enhance the stability of treatment effects.

In this study, we will use Rs-fMRI to explore the alterations in brain functional connectivity before and after TMS treatment for ET, as well as to assess whether FC differs among three distinct groups. Studies have shown disruption in FC between the bilateral cerebellum and the cortex in patients with ET (58, 59). Furthermore, tremor severity may exhibit a positive correlation with FC between cerebellar lobule VI and VIM, as well as between the VIM and the cortex (60). These findings underscore the critical role of the CTC loop in the pathogenesis of ET.

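### The primary change score rests on one pre-treatment occasion against eight later ones; assessing tremor at the existing D0 visit as well, and adjusting for baseline, would gain precision cheaply

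*Protocol article*

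**What the plan says.** Protocol article, Study design: "Electrophysiological detection and TETRAS will be performed at baseline, after the first, fifth, tenth day of treatment (D1, 5, 10", with later assessments up to week 4.

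Protocol article, Primary outcome: "The primary outcome measure will be the mean change from baseline over the course of 4 weeks", taken "at days 1, 5, 10, D10-24 h, then at weeks 1, 2, 3, and 4". That is eight post-baseline occasions.

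Table 1 (Study design) marks TETRAS and tremor analysis once before treatment, at D1-B, which its footnote defines as "D1-B, Before the first day of treatment". The D0 screening column includes MRI and vital signs, but both tremor measures are blank there.

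Accelerometer-based tremor analysis: "Each movement will be recorded for 20 s, with tremor measurements repeated twice at each time point", and the two recordings are averaged.

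Statistical analysis: "We will employ generalized estimating equations (GEE) for repeated measures within the modified ITT population". No baseline term is named for that model. The baseline tremor score appears only among the covariates of a sensitivity analysis.

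The Discussion says that essential tremor has "potential inter- and intra-individual differences, where factors such as anxiety (55), fatigue (56), and caffeine consumption (57) can all influence the severity of tremors".

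**The concern.** A mean over eight visits averages out visit-to-visit noise in tremor. A single baseline does not, and its error is carried into all eight change scores of that patient. By the article's own account, tremor moves with a patient's state, so this noise is unlikely to be negligible.

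The two accelerometer recordings are made at the same time point. Averaging them reduces recording-level noise but not day-to-day noise.

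With eight patients per group, and results meant to inform the Phase 3 sample size, precision is scarce. The schedule puts all replication after treatment starts and none before it, although a pre-treatment visit is already held.

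**Working it through.** **Inputs from the protocol article.** Pre-treatment occasions p = 1 (Table 1). Later occasions k = 8 (Primary outcome). Eight patients per group, 3 × 8 = 24 in total (Sample size). No SD, reliability or power figure is given, so there is no precision figure to reproduce.

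**Assumptions.** Let s² be the visit-to-visit noise variance within a patient, τ² the between-patient variance in true response, and r the correlation between visits. None is given, so ranges are used.

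**1. Share of measurement noise.** With independent visit errors, the noise variance of the mean change is s²(1/p + 1/k).
- One baseline: 1 + 1/8 = 1.125 s². Baseline share 1/1.125 = 88.9%.
- If D1-B and D1-A share one day's noise: (7/8)² + 7/64 = 0.875 s². Share of the shared day 0.766/0.875 = 87.5%.
- With serially correlated noise (assumed half-life 1, 3 or 7 days), the variance of the post-treatment mean is 0.146, 0.230 or 0.394 s². Baseline variance as a share of the two variances is 1/1.146 = 87%, 1/1.230 = 81% or 1/1.394 = 72%.

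**2. Share of total error.** Adding response spread, the share is 1/(1.125 + τ²/s²).

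| τ²/s² | Baseline share of total variance |
|---|---|
| 0.25 | 73% |
| 0.5 | 62% |
| 0.875 | 50% |
| 1 | 47% |
| 2 | 32% |

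The baseline is therefore the majority only while τ² is below 0.875 s².

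**3. Gain from a second baseline, change score.** The noise variance becomes s²(1/2 + 1/8) = 0.625 s². The ratio of new to old variance is (0.625 + τ²/s²)/(1.125 + τ²/s²).
- τ² = 0: 0.556, a cut of 44%
- τ² = 0.5 s²: 0.692, a cut of 31%
- τ² = s²: 0.765, a cut of 24%
- τ² = 2 s²: 0.840, a cut of 16%

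If the D0 and D1-B errors have correlation c, and follow-up errors stay independent of them, the mean of the two has variance s²(1 + c)/2. The 44% then shrinks to 44% × (1 − c). The D0-to-D1 interval is not stated, so c is unknown.

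**4. Gain from a second baseline when baseline is a covariate.** With total variance 1 and s² = 1 − r, the adjusted variance is r + (1 − r)/8 − r²/(r + (1 − r)/p) + τ².
- τ² = 0: r = 0.5 gives 0.3125 to 0.2292 (27%); r = 0.9 gives 0.1025 to 0.0599 (42%).
- τ² = s²: r = 0.5 gives 0.8125 to 0.7292 (10%); r = 0.9 gives 0.2025 to 0.1599 (21%).

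**5. Gain from adjustment alone, one baseline, τ² = 0.** Compared with the change-score variance 1.125(1 − r), the cut is 44%, 27%, 18% and 9% at r = 0.5, 0.7, 0.8 and 0.9. For example, at r = 0.7 the variance goes from 0.3375 to 0.2475.

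**6. Illustration.** n = 8 per arm, r = 0.7, τ² = 0, 80% power, two-sided 0.05. The detectable difference is (1.96 + 0.84) × √(variance) × √(2/8). This is 0.81 SD now, 0.70 SD with one baseline adjusted, and 0.61 SD with two baselines unadjusted. The normal approximation is optimistic at this size.

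**The case against.** One baseline occasion is an ordinary choice, nothing in the article contradicts it, and a pilot that claims no power need not optimise variance. The later visits are also more than replicates: they trace onset and durability, on which the Discussion reports conflicting earlier results. Both points stand, and they limit this to an improvement in precision.

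The planned sensitivity analysis already adjusts for the baseline score. That recovers part of the loss, but not in the primary estimate, and step 4 shows that a second baseline still helps after adjustment.

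A D0 reading could make the baseline worse. The inclusion criteria restrict anti-tremor therapy during the stimulation period only, so D0 and D1-B may differ in medication status. This stands and shapes the fix.

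Four stronger readings are tempting but not supported:
- **That baseline noise dominates the whole error of the primary outcome.** This needs τ² below about 0.9 s². The documents give neither variance, and the Discussion stresses differences between individuals.
- **That the accelerometer baseline is a single reading.** It is one occasion with two averaged recordings, and accelerometry is a secondary outcome.
- **That anxiety just before the first session biases the result.** Table 1 does not say how long before treatment D1-B falls. A raised baseline would affect all randomised, patient-blinded arms alike in expectation. It could inflate change within an arm, but that is conjecture.
- **That a follow-up reading such as D10-A could be given up in exchange.** D10-A pairs with the D10 MRI, and day 10 is named in the primary outcome.

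**Conclusion.** The point holds as a loss of precision, not as a bias or a failure of validity. One occasion supplies about 89% of the measurement-noise variance of the mean change if visit errors are independent, and about 72% to 87% under the serial correlation tried. Whether it is most of the total error cannot be settled from the documents.

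A second baseline cuts the variance of the mean change by 44% at best, and by 16% if response variance is twice the visit noise. With baseline as a covariate, the cut is about 10% to 42% for response variance from one times the visit noise down to none and r from 0.5 to 0.9. All of these figures assume equal error variance at every visit and independent errors between D0 and D1-B. They apply in full only to patients who have both readings.

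**What to change.** - In Table 1, add TETRAS and tremor analysis at D0.
- Define baseline as the mean of D0 and D1-B where both are recorded under the same medication status, and record that status at each. Otherwise keep D1-B as baseline and use D0 as a covariate.
- Patients already enrolled keep their single D1-B value. State in advance how they are handled wherever D0 is used, and add a sensitivity analysis with D1-B alone as baseline for everyone.
- Move the baseline tremor score from the sensitivity analysis into the primary GEE. This needs no new data.
- Keep D10-A.

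Cost: an amendment to Table 1 and the Statistical analysis section, and one more rating and recording session per patient at a visit already held. Because recruitment is ongoing, the trial will mix one- and two-occasion baselines with different error variances. The gain falls with every patient enrolled before the change.

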### Participants and recruitment

2.2

Participants will be recruited from the Department of Neurology, the First Affiliated Hospital of Xi’an Jiaotong University, with reference to the diagnostic criteria for ET established by the International Movement Disorders Society in 2020 (6); The diagnosis of ET will be made independently by two professors specializing in movement disorders in the Department of Neurology. All the participants should sign informed consent. The study protocol is approved by the Ethics Committee of the First Affiliated Hospital of the Xi’an Jiaotong University.

#### Inclusion criteria

2.2.1

Males or females, ages from 18 to 80 years;Meet the diagnostic criteria for ET with visible upper limbs tremor;The participants are qualified to complete the scales and perform a physical neurological examination. They should not receive any anti-tremor therapy during the stimulation period;Signed written informed consent.

#### Exclusion criteria

2.2.2

Participants with severe neuropsychiatric disease such as schizophrenia, bipolar disorder, and major depressive disorder.Have a clinically significant abnormality on the screening examination that might affect safety, study participation, or confound the interpretation of study results;Participants with contraindications to MRI, such as those with metal implants in their bodies;Severe migraine, cranial injury, suicide risk, or epilepsy risk.

### TMS stimulation

2.3

